## Abstract

**Introduction:**

Pre-eclampsia is a condition associated with significant maternal and neonatal morbidity and mortality. The prediction of pre-eclampsia in high-risk populations using angiogenic markers, such as serum placental growth factor (PlGF) assessment, has been shown to improve maternal outcomes and is recommended by the National Institute for Health and Care Excellence (NICE). However, such tests are not yet available at the point of care (POC). Glycosylated fibronectin (GlyFn) level for the prediction of pre-eclampsia development is available as a POC test (Lumella) and has the potential to aid rapid clinical decision making. This study aimed to test the hypothesis that the sensitivity of the GlyFn test is not inferior to that of the current gold standard of soluble fms-like tyrosine kinase (sFlt)/PlGF-based laboratory testing for pre-eclampsia.

**Methods and analysis:**

This is a multicentre prospective study. Women at risk for pre-eclampsia based on predefined clinical and/or obstetric risk factors will be invited to participate in the study. The recruitment target is 400 participants. Consenting participants will have paired samples for sFlt/PlGF together with POC GlyFn testing. Two follow-up visits are planned at 2 and 4 weeks after the initial recruitment where repeat testing with both tests will be performed. The clinical team will be blinded to the results of the GlyFn test but not that of the sFlt/PlGF test. Clinical care will be based on established protocols incorporating maternal/fetal evaluation and the results of sFlt/PlGF levels. Maternal and neonatal outcome data will be collected to compare the sensitivity and specificity of the tests, with the primary outcome being delivery for pre-eclampsia within 4 weeks.

**Ethics and dissemination:**

Ethical approval has been obtained from the Health Research Authority and Health and Care Research Wales Ethics Committee. The results of this study will be published in peer-reviewed journals and presented at scientific conferences.

**Trial registration number:**

ISRCTN13430018

STRENGTHS AND LIMITATIONS OF THIS STUDYThis diagnostic test accuracy study used a paired design for the head-to-head comparison with the current gold standard test.The results of the Lumella test will be unknown to the clinical team and will not influence decision making.The clinical team will have the results of placental growth factor-based testing if available, which may introduce intervention bias.

## Introduction

 Pre-eclampsia complicates 3%–6% of pregnancies, with a 1.5-fold to a 2.0-fold higher incidence in first pregnancies and pregnancies with multiple gestations.^1^,^3^ Pre-eclampsia also has a significant impact on overall healthcare costs. A recent analysis reported that the short-term costs of pre-eclampsia in the USA in 2012 were over $2 billion.^4^ Globally, pre-eclampsia is associated with 10%–15% of all maternal deaths during pregnancy and childbirth, making it the second-leading cause of maternal mortality, resulting in an estimated 76 000 maternal deaths annually.^5 6^ Adverse maternal outcomes can be mitigated by early diagnosis, early delivery and appropriate intrapartum management. Early delivery unfortunately exposes the neonate to short-term and long-term adverse outcomes associated with prematurity. Clinical judgement and provider expertise are required to balance maternal versus neonatal risks. An effective, cost-efficient diagnostic tool would be valuable to aid decision-making. Previous studies have suggested that mortality rates could be considerably reduced if clinicians were made aware of the high likelihood of pre-eclampsia development.^7 8^

Pre-eclampsia was redefined by the American College of Obstetricians and Gynaecologists in 2013 and re-affirmed in 2019.^9 10^ Specifically, the ‘traditional’ diagnostic criteria of new-onset hypertension (>140/90 mm Hg and proteinuria >300 mg/24 hours after 20 weeks of gestation) were revised, and proteinuria is no longer required if other maternal organ dysfunction (ie, renal insufficiency, liver involvement, and neurological and haematological complications) is present. Other international studies have also added uteroplacental dysfunction or intrauterine growth restriction to the diagnostic criteria for pre-eclampsia.^11 12^ Eclampsia and the syndrome of haemolysis, elevated liver enzymes and low platelets (HELLP) can also occur in the absence of hypertension or proteinuria.^13 14^ These ‘non-traditional’ constellations of symptoms contribute to the difficulty in obtaining an accurate diagnosis of pre-eclampsia based solely on clinical criteria. The latest recommendations from the International Society for the Study of Hypertension in Pregnancy advise the use of ‘markers of angiogenic imbalance’ when evaluating women at risk for pre-eclampsia.^11^ Preterm pre-eclampsia carries a higher risk than term pre-eclampsia. It is associated with higher rates of progression to severe pre-eclampsia with an increased risk of maternal as well as fetal/neonatal morbidity and morbidity.^15 16^

An important supplement to diagnoses based on observable clinical presentation is the determination of the levels of specific biomarkers that can be measured in body fluids such as blood or urine. Several circulating factors are associated with pre-eclampsia, including soluble endoglin, placental growth factor (PlGF), soluble fms-like tyrosine kinase-1 (sFlt-1), vascular endothelial growth factor, pregnancy-associated plasma protein A-2, vasopressin, copeptin and glycosylated fibronectin (GlyFn).^17^,^21^ Although many of the above markers have shown changes in pregnancies affected by pre-eclampsia prior to onset and after the detectable onset of the condition, only some have been validated for routine clinical use to assess pre-eclampsia. A high serum level of maternal GlyFn is proposed as a highly sensitive and specific biomarker for pre-eclampsia, making it a useful adjunct diagnostic test in the evaluation of new-onset hypertension in pregnancy.^1722^,^25^ The availability as a point of care (POC) test makes it suitable for use, particularly for triage and in high-resource and low-resource settings. The Lumella GlyFn test uses a maternal finger-stick blood sample to determine the levels of a specific glycosylated form of fibronectin as a biomarker for pre-eclampsia. It has been proposed as an alternative to the sFlt-1/PlGF ratio for the assessment of the risk of developing pre-eclampsia within 2 and 4 weeks of testing.^26^ The majority of evidence for the utility of the glycosylated fibronectin test is based on retrospective studies using stored samples.

This clinical study will prospectively evaluate the quantitative POC measurement of GlyFn in maternal blood. The test will be used as an aid in the risk assessment of women with clinical findings suggestive of pre-eclampsia, in conjunction with other clinical and laboratory information. This study is designed to bridge the current gap in evidence around the effectiveness of POC GlyFn testing in the diagnosis and clinical triage for pre-eclampsia and compare performance against the current standard of care. The availability of such tests can have an impact on reducing maternal and neonatal risks associated with severe pre-eclampsia.

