## Methods

### Recruitment and sampling

This prospective multicentre observational study will be conducted at St George’s Epsom and St Helier University Hospital Trusts in the UK. Recruitment started in January 2024 and is planned to last over 18 months.

The study uses predefined eligibility criteria to identify the population at risk of pre-eclampsia (table 1). Participants will undergo paired testing for the Lumella test and PlGF-based testing (Roche sFlt/PlGF test) at recruitment and in 2 and 4 weeks by the research staff. The clinical team will be blinded to POC test results. Participant information sheet and consent form are provided in onlinesupplemental files 1  2.

**Table 1 T1:** Eligibility criteria for inclusion

Clinical risk factors (Requires on one risk factor)	
	Systolic blood pressure ≥130 mm Hg on one or more occasions
	Diastolic blood pressure ≥85 mm Hg on one or more occasions
	Elevated urinary protein
	Urine protein dipstick test 1+ or more
	Urinary protein/creatinine ratio ≥0.30 mg/mg
	Urinary protein ≥300 mg per day in timed collection
	New-onset low platelet count ≤100 000 x 109 /L
	New-onset elevated serum creatinine ≥1.0mg/dL
	New-onset transaminase elevation above the limits of normal for local laboratory
	New-onset headache unresponsive to medication and not accounted for by alternative diagnoses
	New-onset visual symptoms
	Fetal growth restriction with estimated fetal weight ≤10th percentile
Historical/obstetrical risk factors	
	History of pre-eclampsia
	Multifetal presentation
	Pre-existing hypertension
	Pre-gestational diabetes mellitus
	Pre-existing renal disease

In the UK, current NICE recommendations advise performing PlGF-based testing in cases presenting with suspected pre-eclampsia to aid in diagnosis and outcome prediction. However, test results should not be used to make decisions for delivery in isolation, and full clinical and laboratory assessment should be considered.^27^

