### Secondary/subgroup analyses

Secondary analysis will estimate the positive and negative predictive values (PPV and NPV, respectively) for the detection of pre-eclampsia within 4 weeks of sampling for the POC GlyFn test, sFLT/PlGF ratio and POC plasma PlGF (Quidel) test. The PPV and NPV, along with the 95% confidence rectangle (ie, CIs for each metric estimated jointly), will be computed under various pre-eclampsia prevalence assumptions, including the prevalence observed in the current study, as well as lower/higher estimates reported in the literature. The optimum cut-off value of the Lumella test will be determined for testing the non-inferiority hypothesis for the sensitivity to the primary outcome (delivery for pre-eclampsia within 4 weeks of the first test).

Furthermore, secondary analyses will be conducted by substituting (a) pre-eclampsia within 2 weeks of sampling, (b) development of pre-eclampsia with severe features (yes/no), and (c) preterm delivery (yes/no) into the cross-tabulation instead of pre-eclampsia (yes/no).

In addition, the time to development of PE and time to delivery for subjects with low-risk and high-risk results (based on the derived test cut-off) will be assessed using Kaplan-Meier curves and Cox proportional hazards models. All analyses will be re-performed based only on certain prespecified subgroups, such as women with chronic hypertension at baseline, gestational age (<34 or ≥34 weeks), interventions and presence of gestational diabetes.

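### The test is meant for women with clinical findings suggestive of pre-eclampsia, but women with only a historical or obstetric factor appear eligible and are pooled with them, so pooled specificity and PPV may not describe the intended-use group

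*Protocol article*

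**What the plan says.** **Intended use.** The Protocol article, Introduction, describes the test as "an aid in the risk assessment of women with clinical findings suggestive of pre-eclampsia" and aims to fill a gap in evidence on diagnosis and triage against the standard of care. Under Recruitment and sampling, national guidance is said to "advise performing PlGF-based testing in cases presenting with suspected pre-eclampsia". Use and comparator are thus both placed in suspected disease.

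**Who is enrolled.** The abstract (Methods and analysis) states: "Women at risk for pre-eclampsia based on predefined clinical and/or obstetric risk factors will be invited to participate in the study". Recruitment and sampling says: "The study uses predefined eligibility criteria to identify the population at risk of pre-eclampsia". Table 1 has two blocks. The first is headed "Clinical risk factors (Requires on one risk factor", with garbled wording. The second, "Historical/obstetrical risk factors", lists previous pre-eclampsia, multifetal pregnancy, pre-existing hypertension, pre-gestational diabetes and renal disease. It has no entry rule and does not say that a clinical finding is also needed.

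**How they are analysed.** Primary objective analysis uses one cross-tabulation for sensitivity and specificity, with the GlyFn threshold derived from the study cohort. Secondary/subgroup analyses plans PPV and NPV at several prevalences, and subgroups such as "women with chronic hypertension at baseline, gestational age (<34 or ≥34 weeks), interventions and presence of gestational diabetes".

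**The concern.** The population the test is to serve and the population in the accuracy table are not the same. A well, normotensive woman with a previous pre-eclamptic pregnancy would count in the table equally with a woman presenting with hypertension and headache.

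The named subgroups do not separate the two. Chronic hypertension can be present in either route. Gestational diabetes is not a Table 1 criterion, since the table lists pre-gestational diabetes. Gestational age and interventions cut across both routes.

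If specificity differs by route, the pooled figure depends on how many women of each kind happen to be recruited. It, and any PPV calculated from it, need not apply to women with suspected pre-eclampsia. The planned recalculation of PPV at other prevalences carries the pooled specificity along and so cannot correct this.

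**Working it through.** **The plan's own figures.** The article gives no accuracy, event rate or recruitment share by route of entry, so there is no figure of this kind to reproduce. Its relevant numbers are 400 women and a 23% prevalence (400 × 0.23 = 92 cases). Every other value below is an assumption.

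**Formulas.**
- Pooled specificity = true negatives in both groups / non-cases in both groups.
- NPV = Sp(1−p) / [Sp(1−p) + (1−Se)p].
- PPV = Se·p / [Se·p + (1−Sp)(1−p)].

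**1. Direction of the specificity shift.** Assume specificity 0.80 and prevalence 23% with clinical findings, prevalence 5% in history-only women, and 25% history-only. The non-case weights are 0.75 × 0.77 = 0.5775 and 0.25 × 0.95 = 0.2375, total 0.815.

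| History-only specificity | Pooled specificity | Clinical-findings group |
|---|---|---|
| 0.95 | (0.462 + 0.2256)/0.815 = 0.844 | 0.800 |
| 0.80 | 0.800 | 0.800 |
| 0.70 | (0.462 + 0.1663)/0.815 = 0.771 | 0.800 |

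With history-only shares of 10% to 50% and history-only prevalence of 5% or 10%, pooled specificity runs from 0.745 to 0.883. The sign depends on a quantity the documents do not give.

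**2. One scenario in full.** Assume 40% history-only. Clinical-findings women: 20% events, sensitivity 85%, specificity 80%. History-only women: 3% events, sensitivity 70%, specificity 95%.

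- Clinical findings, 240 women: 48 cases (40.8 detected, 7.2 missed); 192 non-cases (153.6 true negatives).
- History only, 160 women: 4.8 cases (3.36 detected, 1.44 missed); 155.2 non-cases (147.4 true negatives).
- Pooled sensitivity: 44.16/52.8 = 83.6%.
- Pooled specificity: 301.0/347.2 = 86.7%, against 80%.
- NPV as observed: 301.0/(301.0 + 8.64) = 97.2%, against 153.6/160.8 = 95.5%.

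**3. Effect of the planned prevalence recalculation.** Apply the pooled sensitivity and specificity at the clinical group's 20%.

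- NPV: 0.6936/(0.6936 + 0.0327) = 95.5%, equal to the clinical-findings value. The gap closes.
- PPV: 0.1673/(0.1673 + 0.1064) = 61%, against 0.17/(0.17 + 0.16) = 52%. The gap remains, because it comes from specificity.

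Across the range in step 1 (sensitivity 0.85 in both groups), NPV from the pooled specificity at 23% prevalence is 0.943 to 0.952, against 0.947 in the clinical-findings group.

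**4. Primary sensitivity comparison.** Non-cases do not enter sensitivity. In the step 2 scenario, history-only women supply 4.8/52.8 = 9% of cases, so the pooled paired difference is 0.91 × (difference in the clinical group) + 0.09 × (difference in the history-only group). If those two differences were 10 points apart, the pooled value would move by 0.9 point. The same women supply 155.2/347.2 = 45% of non-cases. If the choice of cut-off gives weight to specificity, they could influence it far more than they inform sensitivity.

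**The case against.** A reader might infer that the pooled cohort is simply an easier population, so that specificity and NPV will be inflated. The documents do not support that. They give no specificity or event rate by route, and factors such as renal disease, pre-existing hypertension or multifetal pregnancy could act either way. For NPV, the planned prevalence recalculation removes nearly all of the gap. These objections stand.

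It can also be said that the cohort is described throughout as at-risk or high-risk, that an at-risk cohort is a legitimate choice, and that the intended use rests on one sentence of the Introduction. That is fair as to the design, and is why the pooled primary analysis should stay. But the same article places the comparator in suspected disease and names triage as an aim, so it works with two populations.

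The primary hypothesis is paired sensitivity with both tests run in the same women, so case mix is identical for the two tests. This stands, subject to the cut-off.

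The subgroup list is open-ended, and a full protocol or SAP may add the split. That is possible. It does not resolve the mismatch between stated use and entry criteria, which is fixed in this article.

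Finally, the garbled note in Table 1 leaves room for a reading in which a clinical factor is always required. If that is meant, the abstract contradicts it, and the text needs repair either way.

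**Conclusion.** The point holds in a limited form. The stated use and the enrolled population differ, both routes of entry are pooled, and no named subgroup separates them. Pooled specificity and PPV may therefore differ from their values in women with clinical findings, in a direction and by an amount that the documents do not determine. Under the assumed values the specificity difference is from about 5 points lower to 8 points higher (0.745 to 0.883 against 0.800). In the 40% scenario, PPV at 20% prevalence is 61% against 52%.

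NPV is largely dealt with by the plan. The primary non-inferiority comparison is little affected as long as history-only women supply few of the cases; the cohort-derived cut-off is the one route by which their non-cases could matter. The study is not invalidated. What is at stake is whether its specificity and PPV can be quoted for triage of suspected pre-eclampsia.

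All of this assumes that a historical or obstetric factor alone qualifies, which the abstract says and Table 1 leaves unclear.

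**What to change.** 1. Reconcile Table 1 with the abstract so that both state the same rule on whether a historical or obstetric factor alone qualifies.
2. Keep the pooled primary analysis. Recruitment began in January 2024, and a change of primary population is not needed.
3. If a historical factor alone qualifies, add to Secondary/subgroup analyses a prespecified report of sensitivity, specificity, PPV, NPV and the paired comparison for two groups: at least one Table 1 clinical finding at the first test, and historical/obstetric factor only.
4. Limit statements about triage of suspected pre-eclampsia to what the first group shows.

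**Cost.** A few sentences. Eligibility checks should already establish the qualifying factor, although the article does not say that it is recorded for each woman; this should be confirmed.

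Precision falls within the clinical-findings group. In the 40% scenario the standard error of specificity rises from √(0.867 × 0.133/347.2) = 1.8 points to √(0.80 × 0.20/192) = 2.9 points. At a 60% history-only share it rises from about 1.6 to 3.5 points. Specificity in the clinical-findings group may also prove less favourable than the pooled figure.

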## Methods

### Recruitment and sampling

This prospective multicentre observational study will be conducted at St George’s Epsom and St Helier University Hospital Trusts in the UK. Recruitment started in January 2024 and is planned to last over 18 months.

The study uses predefined eligibility criteria to identify the population at risk of pre-eclampsia (table 1). Participants will undergo paired testing for the Lumella test and PlGF-based testing (Roche sFlt/PlGF test) at recruitment and in 2 and 4 weeks by the research staff. The clinical team will be blinded to POC test results. Participant information sheet and consent form are provided in onlinesupplemental files 1  2.

**Table 1 T1:** Eligibility criteria for inclusion

Clinical risk factors (Requires on one risk factor)	
	Systolic blood pressure ≥130 mm Hg on one or more occasions
	Diastolic blood pressure ≥85 mm Hg on one or more occasions
	Elevated urinary protein
	Urine protein dipstick test 1+ or more
	Urinary protein/creatinine ratio ≥0.30 mg/mg
	Urinary protein ≥300 mg per day in timed collection
	New-onset low platelet count ≤100 000 x 109 /L
	New-onset elevated serum creatinine ≥1.0mg/dL
	New-onset transaminase elevation above the limits of normal for local laboratory
	New-onset headache unresponsive to medication and not accounted for by alternative diagnoses
	New-onset visual symptoms
	Fetal growth restriction with estimated fetal weight ≤10th percentile
Historical/obstetrical risk factors	
	History of pre-eclampsia
	Multifetal presentation
	Pre-existing hypertension
	Pre-gestational diabetes mellitus
	Pre-existing renal disease

In the UK, current NICE recommendations advise performing PlGF-based testing in cases presenting with suspected pre-eclampsia to aid in diagnosis and outcome prediction. However, test results should not be used to make decisions for delivery in isolation, and full clinical and laboratory assessment should be considered.^27^

### Inclusion and exclusion criteria

Potential participants are those with a gestational age between 24^+0^ and 36^+6^ if they are aged 18 or over with plans to deliver at the study site. The exclusion criteria are as follows: diagnosis of pre-eclampsia at the time of enrolment, planned delivery prior to 37^+0^ weeks for other clinical reasons or pregnancies with known/suspected major fetal structural or chromosomal abnormality.

### Sample size calculation

A total of 400 participants will be recruited across the study sites. Sample size of the cohort was estimated using a formula described by Alonzo *et al*^28^ for demonstrating the non-inferiority of the POC GlyFn test (Lumella) compared with PIGF and sFlt/PIGF for pre-eclampsia prediction, with sensitivity as the primary endpoint at a non-inferiority margin of 5%. The prevalence of pre-eclampsia in this high-risk population was estimated to be 23% according to data from the INSPIRE study.^29^

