### Primary and secondary outcomes

The *primary outcome* is delivery for confirmed pre-eclampsia within 4 weeks of testing.

The *secondary outcomes* include diagnosis of pre-eclampsia within 7 and 28 days of sampling, severe gestational hypertension, severe preterm pre-eclampsia, severe maternal complications (cerebrovascular accidents, pulmonary oedema, renal failure or HELLP) and preterm birth.

A composite perinatal mortality/neonatal morbidity score will be assigned based on information captured including survival status at 28 days or discharge (whichever occurs first) and clinical complications including admission to the neonatal intensive care unit, respiratory distress syndrome, bronchopulmonary dysplasia, intraventricular haemorrhage, retinopathy of prematurity, necrotising enterocolitis requiring surgery and days of assisted ventilation.

All outcome data will be collected from hospital records of participants and their newborns.

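### The sample size is built on prevalence of pre-eclampsia, a broader event than the primary outcome, and even the implied 92 cases give 80% power at a 5-point margin only if two equally sensitive tests disagree in about 3% of cases or fewer

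*Protocol article*

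**What the plan says.** The Sample size calculation section of the protocol article fixes the size: "A total of 400 participants will be recruited across the study sites". It ties that number to showing that the GlyFn test is non-inferior, "with sensitivity as the primary endpoint at a non-inferiority margin of 5" per cent. The only event rate it gives is this: "The prevalence of pre-eclampsia in this high-risk population was estimated to be 23% according to data from the INSPIRE study".

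Under Primary and secondary outcomes, the primary outcome is "delivery for confirmed pre-eclampsia within 4 weeks of testing". The same section lists "diagnosis of pre-eclampsia within 7 and 28 days of sampling" separately, as a secondary outcome. The Secondary/subgroup analyses section sets the time origin for the non-inferiority test: "delivery for pre-eclampsia within 4 weeks of the first test".

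On who enters, the Abstract says: "Women at risk for pre-eclampsia based on predefined clinical and/or obstetric risk factors will be invited to participate in the study". Women already diagnosed at enrolment are excluded, and entry is open from 24+0 weeks.

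**The concern.** Sensitivity has only cases in its denominator, so the precision of the non-inferiority comparison depends on how many women reach the primary outcome, not on the 400 recruited. The rate used for sizing describes a different and broader event. A woman who enters early in the window, perhaps on obstetric history alone, can develop pre-eclampsia months later. She would then count towards a prevalence of pre-eclampsia but not towards the primary outcome.

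A 5-point margin is also narrow for about 90 cases: 5% of 92 is 4.6 women. In a paired comparison the width of the interval is driven by the cases on which the two tests disagree, and few disagreements are needed to make it wider than the margin.

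At stake is how the primary result is read. If GlyFn is exactly as sensitive as the comparator and the trial still misses the margin, readers who believe the study was sized for that margin may take the miss as evidence against GlyFn.

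**Working it through.** **Inputs from the article.** Total 400; rate 23%; margin 5% on sensitivity; one test pair per woman for the primary analysis, because the outcome is dated from the first test.

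**Assumed, because the article does not state them.** One-sided alpha 2.5%, with 5% as the lenient variant; 80% power; equal true sensitivity; margin on the difference scale, with a ratio variant; discordance (share of cases on which the tests disagree) of 5%, 10% and 20%; no dropout.

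**Step 1: can 400 be reproduced?** Not forward, since alpha, power, sensitivities and discordance are not given. The calculation is therefore solved backwards for the discordance at which 400 suffices.

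**Step 2: cases.** 0.23 × 400 = 92. If 23% counts any pre-eclampsia, this is the most that can be expected for the primary outcome.

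**Step 3: largest discordance that 92 cases can carry.** With n cases, discordance ψ and margin δ, equal sensitivities give ψ_max = n δ² / (z_α + z_β)².

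- One-sided 2.5%: 92 × 0.0025 / (1.960 + 0.842)² = 0.23 / 7.849 = 2.9%, or 2.7 women.
- One-sided 5%: 0.23 / (1.645 + 0.842)² = 0.23 / 6.183 = 3.7%, or 3.4 women.
- Ratio margin of 0.95, one-sided 2.5%: 92 × (ln 0.95)² × Se² / 7.849, where Se is the common sensitivity, gives 2.0% at Se 0.80 and 2.8% at Se 0.95.

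**Step 4: power at wider discordance.** Power = Φ(0.05 × √(n/ψ) − z_α). For example, with n = 92 and ψ = 0.10, 0.05 × √920 = 1.517; 1.517 − 1.960 = −0.443; Φ = 33%.

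| Cases | One-sided alpha | ψ = 5% | ψ = 10% | ψ = 20% |
|---|---|---|---|---|
| 92 (23%) | 2.5% | 57% | 33% | 19% |
| 92 (23%) | 5% | 69% | 45% | 28% |
| 60 (15%, assumed) | 2.5% | 41% | 23% | 14% |
| 40 (10%, assumed) | 2.5% | 29% | 17% | 11% |

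The last two rows only illustrate fewer cases; the documents give no rate for the primary outcome. A simulation with the paired score test gave lower power than this formula: 44% at 5% discordance and 27% at 10%, with 92 cases at one-sided 2.5%.

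**Step 5: margin that 92 cases can resolve with 80% power (one-sided 2.5%).** δ = 2.802 × √(ψ/92).

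- ψ = 10%: 2.802 × 0.0330 = 9.2 points.
- ψ = 20%: 2.802 × 0.0466 = 13.1 points.

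**Step 6: if GlyFn is truly more sensitive by d.** ψ_max = n(δ + d)² / 7.849 + d². For d = 5 points: 92 × 0.01 / 7.849 + 0.0025 = 12.0%. At d = 5 points and ψ = 10%, power is Φ(0.10 × √(92 / 0.0975) − 1.960) = Φ(1.112) = 87%.

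**The case against.** The strongest reply is that the calculation rests on equal sensitivity, which the article does not fix. Step 6 shows that a true 5-point advantage for GlyFn would give good power at 10% discordance. That stands as a condition on the result. The article also derives the GlyFn cut-off from the study cohort, so a threshold favouring sensitivity is possible. But an advantage obtained by choosing the threshold on the same data is not a planning justification, and the stated hypothesis is non-inferiority.

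The second reply is that the article is a condensed account. Alpha, power, expected sensitivities and discordance may be in the full protocol or SAP, and their absence here is not counted as a fault. Nor can the derivation of 400 be called an arithmetic error, since its inputs are not visible. What remains is that every conventional alpha and either margin scale tried above leads to the same narrow limit.

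Repeat visits might seem to help. Treating all three as independent would give at most 276 pairs and a limit of 8.8% at one-sided 2.5%. But repeat tests in one woman are not independent, and the outcome is tied to the first test.

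Four stronger readings are tempting, and the documents do not support them:

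- A reader might infer that 400 women cannot show non-inferiority at all. The result is only that power falls below 80% when sensitivities are equal; at 5% discordance it is still 57% to 69%.
- A reader might infer that the tests are bound to disagree in more than 3% of cases. It is reasonable to doubt such close agreement between different biomarkers, but the article gives no discordance or sensitivity for either test, so the range is an assumption.
- A reader might infer a definite shortfall below 92. The time window behind the 23% is not shown, so its size cannot be derived.
- A reader might infer that two discordant women in each direction would already fail the test. The paired score z is then 1.78, but the Wald z is 0.05 / (√4 / 92) = 2.30, and the article fixes neither the test statistic nor alpha.

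**Conclusion.** The point holds in a conditional form. The sizing rate belongs to a broader event than the one in which sensitivity is computed, so 92 expected cases is a ceiling if 23% counts any pre-eclampsia. At that ceiling, with truly equal sensitivities, the stated margin is matched by 80% power only when the tests disagree in about 3% of cases or fewer: 2.9% at one-sided 2.5%, 3.7% at one-sided 5%. Over the assumed range of 5% to 20% discordance, power runs from 57% down to 19%, or from 69% down to 28% at one-sided 5%. Fewer cases lower these figures; only a true GlyFn advantage raises them.

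The mismatch of events follows from the text alone. The power figures rest on the assumed alpha, power target and discordance and on equal sensitivity. Under those ordinary planning assumptions, the stated size does not deliver the purpose given for it.

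**What to change.** Keep 400 and change three things.

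1. Redo the calculation with the expected rate of the primary outcome, counted from the first test, in place of 23%.
2. Replace the claim that 400 is sized for 5% non-inferiority with the power actually available over a labelled discordance range, and with the margin that can be resolved at 80% power: about 9 points at 10% discordance and 13 at 20% with 92 cases, wider with fewer.
3. Report the paired difference in sensitivity with its 95% confidence interval as the main result, and state that an interval crossing the 5-point margin is inconclusive rather than a finding of inferiority.

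The cost is one rewritten paragraph and a change of emphasis in reporting, with no extra women. The downside is that the study's stated capability becomes less favourable.
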